#### Exclusion criteria

Exclusion criteria will be patients (1) that fail to give written informed consent, (2) with uncontrolled epilepsy, (3) with pacemaker or any metallic object implanted in the brain, (4) who are pregnant or breastfeeding, (5) that have hemineglect or severe attentional problems (omission of more than 15 bells on the Bell’s test [29]), (6) with aphasia of comprehension dysfunction (Boston Diagnostic Aphasia Examination < 4/5 [36]), (7) with severe cognitive dysfunction (Mini Mental State Examination-MMSE < 24 [35]), (8) not covered by a French social security scheme, and (9) under guardianship.

#### Settings and recruitment

Patients will be recruited from in-patient and out-patient clinics at the physical and rehabilitation medicine (PRM) departments of the two university hospitals (CHU): Lapeyronie (Montpellier, France) and Nîmes (Grau du Roi, France). Before including patients in the ReArm protocol, the medical physician taking care of the patient will check if the patient fits with the inclusion criteria and does not present any exclusion criteria during a usual clinical outpatient visit. The adherence of patients will be improved by an in-patient rehabilitation stay (patients will sleep at the hospital during training days). The investigators will be available any time to explain to the patient the objective of this project.

### Study design

Figure 1 shows a flow diagram of the study design. The ReArm project is a quadruple-blinded, randomized, sham-controlled, bi-centre, two-arm parallel, and interventional study. All patients will undergo 3 weeks of a standard in-patient stroke rehabilitation program (see details in the next section) and will thereafter be followed over a period of 3 months. One group (intervention) will receive 3 weeks rehabilitation consisting of standardized conventional therapy rehabilitation and combined VRT and anodal HD-tDCS. The second group (placebo) will receive standardized conventional therapy rehabilitation and combined VRT and sham HD-tDCS.

**Fig. 1 Fig1:**
[figure not shown]
Flow chart of the study design

#### Randomization

The Capture System software (Ennov Clinical, module randomization, Paris, France) will be set up by the randomization administrator, from the Innovation and Research Department of the Hospital, to give a blinding code to each patient. A centralized randomization will be performed using the Capture System software (Ennov Clinical, module randomization, Paris, France). A minimization algorithm will assure the balance of groups regarding PRM centres (CHU Montpellier or Nimes) and stroke severity (FM-UE score lower or higher than 40 [72]); see “Blinding of group and stimulation protocols” section for more details. For each inclusion, another hospital department, the clinical investigation centre, will use the software to allocate the right protocol.

### Standard in-patient stroke rehabilitation program

Both the intervention and placebo groups will follow the standard in-patient stroke rehabilitation program usually proposed to stroke hemiparetic patients at the Montpellier and Nimes PRM Departments, which includes both conventional therapy and VRT sessions on each day of a 3-week in-patient stroke rehabilitation program. In both PRM departments, VRT has been, since 2014, included in the standard in-patient stroke rehabilitation program.

#### Conventional therapy sessions

Conventional therapy includes physiotherapy (1 × 30 min) and occupational therapy (2 × 30 min) sessions spaced over the morning and early afternoon each day. Each session is adapted to the fatigability and recovery of each patient. The physiotherapy session focuses mainly on trunk balance, sensorimotor exercises, standing balance and walking workout, and muscular and cardio-respiratory reconditioning to effort. The occupational therapy sessions are oriented towards sitting and standing balance workout, sensorimotor exercises for movement restoration, and may include prehension exercise, and mirror therapy. A daily speech therapy session will be added when required (language troubles).

#### Virtual reality therapy (VRT) sessions

In addition to the conventional therapy sessions, each day, patients will receive a 30-min VRT session using an UL exoskeleton (ARMEO®, HOCOMA, Volketswil, Switzerland) providing spring-based anti-gravity support. The ergonomic and adjustable exoskeleton embraces the whole UL, from shoulder to hand and counterbalances the weight of the patient’s UL. The Armeo spring VRT system enables hemiparetic patients to achieve more movements in a 3-dimensionnal workspace than they could usually do without anti-gravity support [53, 69]. The Armeo exoskeleton is connected to a computer displaying meaningful functional tasks (e.g., cleaning a window) on a computer screen. Sensors record the active movements and all joint angles during the therapy session. This semi-immersive VRT provides auditory and visual feedback during and after games training. The virtual environment allows to change the type of games and their difficulty but the main objective of all the games is focused on mobilization of the entire paretic UL with some games also including pro/supination (e.g., flower watering) and grasping with the paretic hand (e.g., egg cracking).

Initially, the patient is comfortably seated on the Armeo system; the display screen is placed 75 cm from the patient and the centre of screen 20 cm below the eyes (Fig. 2). The parameters of the ARMEO® (e.g., exoskeleton arm and forearm lengths, arm and forearm anti-gravity compensation, auto-grip), will be set for each patient on the first day (V1) and will not be changed for subsequent sessions. To counterbalance the weight of the patient’s UL, the upper arm and forearm weight compensation is half for all patients. The UL is straight forward if the patient does not move (rest position).

**Fig. 2 Fig2:**
[figure not shown]
Patient setup on the ARMEO virtual reality therapy system. The ARMEO exoskeleton counterbalances the weight of the patient’s upper limb with springs located on the elbow and wrist joints. The patient in a resting position, ready to begin to play the ladybug game

Figure 3 shows 4 examples of the Armeo VRT rehabilitation games. For all patients, each session will start and end with the *Ladybug* game (Fig. 3a), a speed-accuracy test where the patient has to point to the ladybugs (targets) appearing on the screen as fast as possible. The rehabilitation games during the first 20 min of the session will remain identical for all subjects, with the same program order of 9 rehabilitation games (see Table 1). These 9 games enable patients to use any remaining UL motor function (shoulder, elbow, hand) in a 3D workspace. The 9 games include one 3D game (Reveal Panorama), seven 2D games in frontal or horizontal plane (window mopping, egg cracking, fish catching, popping air bubbles, fruit shopping, stove cleaning, reaction time) and one 1D game (snow balls). The next 10 min will include rehabilitation games selected specifically to each patient’s preferences and abilities (e.g., pro/supination). The therapeutic plan for the final 10 min of the 30-min session (order and type of exercises) will be decided during the first session by the therapist in charge of the patient (trying games with them). Patients will be asked to provide feedback after the first session concerning the difficulty of the games, their ability to achieve them, and their preferences. This will allow the therapist to choose the games of the last 10 min of the session. Each patient will follow the set rehabilitation games program configured to their ability that will remain identical for all subsequent sessions.

**Fig. 3 Fig3:**
[figure not shown]
Examples of ARMEO virtual reality therapy games. **a** Ladybug requires the patient to “catch” a series of 48 Ladybugs appearing one after the other on different parts of the screen with a time limit of 3 min. **b** Windows Mopping requires the patient to clean a window by moving the virtual sponge in 2D workspace to completely reveal a panorama. **c** Egg cracking requires the patient to carefully grasp an egg from a virtual pot and move it to a stove. **d** Reveal panorama requires the patient to move a virtual sponge in 3D workspace to completely reveal a panorama

**Table 1 Tab1:** List of the ARMEO virtual reality therapy games detailing the upper limb joints, movements, and workspace

Name of the games	Joints				Workspace/plane
	Elbow ext./flex.^a^	Shoulder ext./flex.	Shoulder horiz abd./add.^b^	Hand (grasp)	
Windows mopping	X	X	X	X	2D/frontal
Reveal panorama	X	X	X	X	3D/frontal + horizontal
Egg cracking	X	X	X	X	2D/frontal
Fish catching	X	X	X		2D/frontal
Popping air bubbles	X	X	X	X	2D/frontal
Snow balls	X	X			1D/horizontal
Fruit shopping	X	X	X	X	2D/frontal
Stove cleaning	X	X		X	2D/horizontal
Reaction time	X	X	X		2D/frontal

^a^Extension/flexion

^b^Horizontal abduction/adduction

The difficulty of the rehabilitation games will be initially set at the highest level (e.g., smallest size of sponge for the window mopping game, see Fig. 3b) in order to allow improvements in performance over the training sessions. Moreover, if a patient achieves a maximum score of 100% on a game with a time limit, they will be able to further improve their performance reducing the time of the game which will be recorded. Depending on the paretic hand recovery level of the patient, auto-grip will be activated or not. Auto-grip is not activated for patients able to grasp. However auto-grip is activated when the patient just needs to move the UL to the location of the target without requiring a hand grip force to secure the target. The auto-grip will be modified to be off during the rehabilitation program if the hand grip ability of the patient improves. The Armeo software presents online and subsequently records each participant’s performance for each rehabilitation game (i.e., time, game performance). The software also records the kinematic movements of the exoskeleton, which will be used for the ladybug end effector trajectory analysis.

#### Anodal high definition transcranial direct current stimulation (HD-tDCS)

Real tDCS will be delivered to patients randomized in the intervention group (*n* = 29) using the Starstim8 device (Neuroelectrics, Barcelona, Spain). The Starstim8 will deliver a constant direct current to the motor cortex of the ipsilesioned hemisphere using a 4x1 HD-tDCS montage [8, 9, 13, 55]. The active anode electrode will be located on the scalp of the ipsilesional motor cortex (C3 or C4 of the 10–20 system) surrounded by four return electrodes (cathode) located at ~ 4 cm from the anode electrode (Fig. 4). The five HD-tDCS electrodes (NgPiStim, AgCl, 3.14 cm^2^) will be held in place on the scalp using a neoprene cap and each electrode will be filled with electrolyte gel (Signagel, Parker Laboratories, New-Jersey, USA). Patients will receive anodal HD-tDCS (2 mA) during the first 20 min of the VRT session. Current will ramp up from 0 to 2 mA for 30 s, remain constant for 20 min, and ramp-down to 0 for 30 s.

**Fig. 4 Fig4:**
[figure not shown]
Anodal HD-tDCS applied to the ipsilesional primary motor cortex during an ARMEO virtual reality therapy session using the right upper limb. The patient is setup on the ARMEO exoskeleton equipped with the HD-tDCS cap comprising a Starstim NIC-power box delivering the current on the back and 5 electrodes located on the left primary motor cortex in a 4x1 HD-tDCS montage with anode on the C3 location

Patients randomized in the placebo group (*n* = 29) will wear the same equipment during the VRT session and will receive active sham HD-tDCS where the current will ramp up from 0 to 2 mA during the first 30 s, remain constant at 2 mA for 30 s, then ramp-down to 0 during the next 30 s, and remain at 0 for the next 20 min [9, 13]. This kind of active sham procedure provides the same feelings on the scalp as the real HD-tDCS session [8, 9, 55], which has been shown to be an optimal method for blinding of the stimulation [28, 56].

Before and after each 30-min VRT session (real or sham), subjects will be asked a few questions relating to the sensations on the scalp, which will be part of the pain and fatigue assessments (see “Secondary outcome measures” section). More specifically, patients will be asked if they feel any headache, stinging, itch, burn, and pain sensation on the scalp region where the HD-tDCS electrodes were located [8, 9].

#### Blinding of group and stimulation protocols

The randomization administrator of the project will designate 8 stimulation protocols in the NIC2 computer software controlling the Starstim8 device (4 active and 4 sham) and give them a blinded code (A to H). Only the blinded code of the program will be given to the therapist in charge of the rehabilitation to be launched for a specific patient. The Starstim8 device will be set in double-blind mode using the NIC2 software, so that the protocol panel does not show the type of stimulation (active or sham). This way, neither the patient, therapist, investigator, nor outcomes assessor will know which protocol is delivered (quadruple blind study). In order to assess blinding, patients will be asked at the end of the 3 weeks of rehabilitation if they think they were in the real or sham stimulation group. If needed (e.g., severe adverse events), blinding could be unblinded if the patient or the medical staff send a request to the Innovation and Research Department (see “Data management” section for more details).

### Description of testing visits and outcome measures

Table 2 presents the timing of the testing visits and outcome assessment measures. The baseline assessment (pre-test) visit (V1) will take place on the first day of the 3-week in-patient hospital rehabilitation stay. A specialist trained therapist will run the clinical assessments (WMFT, FM-UE, Box and Block Test (BBT), Bell’s test, MMSE, Barthel Index (BI); more details in the “Clinical data and outcome measures” section). Patients UL kinematics and motor cortical region activation will then be evaluated by one of the investigators on three functional motor tasks: a seated reaching task (Proximal Arm Non-Use, PANU), a circular steering task, and the Ladybug game of the Armeo VRT platform used for rehabilitation. The next day (day 2), patients will start the standard in-patient stroke rehabilitation program that will last for 13 complete days (excluding weekends) over 3 weeks.

**Table 2 Tab2:** Study testing visits (V1-3) and outcome assessments

Outcome measures	Inclusion visit	Pre-test (V1)	Post-test (V2)	Retention test (V3, 3 months after V2)
Mini Mental State Examination	X			
Boston diagnostic aphasia examination	X			
Bell’s test	X			
Wolf Motor Function Test		X	X	X
Fugl-Meyer Upper Extremity		X	X	X
Box and Block Test		X	X	X
Barthel Index		X	X	X
Actimetry		X	X	X
Proximal Arm Non-Use (PANU)^a^		X	X	X
Reaching task (Kinematics and EEG/fNIRS)		X	X	X
Circular steering task (Kinematics and EEG/fNIRS)		X	X	X
Lady bug test (Kinematics and EEG/fNIRS)		X	X	X

^a^Proximal Arm Non-Use will be assessed during the reaching task

*EEG* Electroencephalography, *fNIRS* Functional near-infrared spectroscopy

The post-test visit (V2) will take place the last day of the 3 weeks (day 19); the post-test will be identical to the pre-test. The 3-month visit (V3) will take place 3 months after the end of the rehabilitation program (day 19) for a retention test and will be identical to the pre- (V1) and post- (V2) tests.

Patients will be given actimetry bracelets to be worn on each UL to measure UL activity for 7 days before V1, for 7 days after V2, and for 7 days after V3.

### Clinical data and outcome measures

#### Clinical data

Clinical data will be collected by the medical doctor during the routine clinical visit, including date of birth, age, sex, hand laterality before and after the stroke, date of the stroke, delay from the stroke to the inclusion, and characteristic of the brain lesion (type and location). Treatment, medication, and health events will also be reported. The source documents are the original data, sheets, and files, from which the data concerning the research are copied in the electronic case report form (eCRF) by the clinical investigation centre (CIC).

#### Primary outcome measure

##### Wolf Motor Function Test (WMFT)

The Wolf Motor Function Test (WMFT [74]) quantifies the motor ability of the UL through 15 timed and function based tasks (i.e., holding a pen, collect paper clips, prehension test) and 2 strength based tasks (arm lifting and hand grip). The speed at which functional tasks can be completed is measured by performance time and the movement quality when completing the tasks is measured by functional ability. The maximum time allowed to complete an item is 120 s. For functional ability scoring, a 6-point ordinal scale is used where 0 corresponds to “does not attempt with the involved arm” and 5 corresponds to “arm does participate/movement appears to be normal”. The WMFT thus gives four scores: (1) a sum of the function score reflecting the movement quality (0–75), (2) a median time score measuring the movement speed (0–120 s), and (3) arm lifting strength (Kg) and (4) hand grip strength (Kg). For our primary outcome analysis, the mean WMFT time and functional ability change scores between the two groups need to be 1.5–2 s for the timed score and 0.2–0.4 points for the functional ability score to be regarded as a clinically important difference [47].

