### Statistical analysis

#### Sample size

Allman et al. [1] reported that compared to sham, real anodal tDCS (1 mA, conventional montage, ipsilesional motor cortex) combined with 9 days of UL rehabilitation in chronic stroke patients had a moderate effect size *d* = 0.4 on the WMFT at 3 months after the intervention. In the meta-analysis of Chhatbar et al. [16], UL motor recovery (FM-UE) in a chronic stroke population was superior in the group receiving a real tDCS (in comparison to sham) with higher current density and smaller electrode size (large effect size *g* = 1.23). Because we will use anodal HD-tDCS with a higher current density (2 mA) and longer rehabilitation dose (13 days) in chronic stroke patients, we estimate that our protocol should have an effect size of *d* = 0.8 on the WMFT at 3 months. Using an alpha bilateral risk of 5% and a power of 80%, 26 patients per group are needed for analysis. If we count a loss of 10% of the patients, we will have to recruit 58 patients (*n* = 29 per group).

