#### Statistical method

Statistical analysis will be performed using the latest version of the free R software. A *p*-value of 0.05 will be considered significant for all analyses. All outcome measures will be assessed at V1, V2, and V3. The primary outcome will be the difference between both groups (*intervention, placebo*) at V3 on the WMFT. The secondary outcomes will be the changes between V1 and V2 (learning) and between V2 and V3 (retention) for both groups.

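### The protocol does not fix one primary quantity: it leaves open which WMFT score is primary and whether it is a V3 value or a change, while the sample size covers a single test

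*Protocol article*

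**What the plan says.** The section on the Wolf Motor Function Test, under the primary outcome measure, states "The WMFT thus gives four scores": a summed function score (0–75), a median time score (0–120 s), and two strength scores. It then begins a sentence "For our primary outcome analysis, the mean WMFT time and functional ability change scores between the two groups" and attaches a clinically important difference to each of the two: 1.5–2 s for time and 0.2–0.4 points for functional ability. It does not say between which visits the change is taken.

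The Statistical method section says "The primary outcome will be the difference between both groups" at V3 on the WMFT. It names no score, and it lists the V1–V2 and V2–V3 changes as secondary outcomes. The primary outcome analysis section likewise compares the groups on the WMFT at V3, by a t-test or a rank test, without naming a score or using the baseline value. The threshold is general: "0.05 will be considered significant for all analyses".

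The Sample size section uses one standardised difference, d = "0.8 on the WMFT at 3 months", and concludes: "Using an alpha bilateral risk of 5% and a power of 80%, 26 patients per group are needed for analysis". Again no score is named.

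**The concern.** Two things are left open: which WMFT score carries the primary claim, and whether it enters as a V3 value or as a change. The WMFT section points to two scores as changes; the statistical sections point to one unnamed score at V3. No ranking of the scores is given, and no rule says whether one or both must show a difference.

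The error rates depend on this. If a significant result on either score could support the claim, the chance of a false positive exceeds 5%. If both were needed, power falls below the stated 80%. The effect size has the same problem: a d of 0.8 on a V3 value and a d of 0.8 on a change are different assumptions unless the V1–V3 correlation happens to be 0.5.

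**Working it through.** **Inputs from the protocol article.** Two-sided alpha 0.05, power 80%, d = 0.8, 26 per group analysed, 10% loss, 29 per group recruited (Sample size); 0.05 for every analysis (Statistical method); two scores in the primary-analysis sentence (WMFT section). **Assumed, because not given:** correlation between the two scores, 0 to 0.9; V1–V3 correlation, 0.3 to 0.7.

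**1. The plan's own figure.** Two-sample t-test with n = 26 per group:
- noncentrality = d × √(n/2) = 0.8 × √13 = 2.884
- degrees of freedom = 50, critical value = 2.009
- power = 80.7% (n = 25 gives 79.1%, so 26 is the smallest sufficient size)
- loss: 26 / 0.9 = 28.9, rounded up to 29 per group, 58 in total

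The stated size is correct for one test of one quantity.

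**2. Two scores at 0.05 each, either sufficient.** Type I error = 1 − P(|Z1| < 1.96 and |Z2| < 1.96), with (Z1, Z2) bivariate normal at correlation ρ. At ρ = 0 this is 1 − 0.95² = 9.75%.

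**3. Two scores at 0.05 each, both required.** With d = 0.8 on both and 80.7% power for each, joint power is the bivariate normal probability that both statistics pass. At ρ = 0 it is 0.807² = 65%.

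| ρ between scores | Type I error, either suffices | Joint power at n = 26, both required |
|---|---|---|
| 0 | 9.75% | 65% |
| 0.5 | 9.1% | 70% |
| 0.8 | 7.8% | 74% |
| 0.9 | 7.0% | 76% |

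Simulated t-tests with 26 per group agree with both columns to within about half a percentage point.

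**4. Splitting alpha instead.** At 0.025 per score, power per test at n = 26 is 71.6%. Restoring 80% per test needs 31 per group, or 31 / 0.9 = 34.4, that is 35 per group (70 in total) after loss.

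**5. V3 value or change.** Suppose d = 0.8 is on the V3 scale, r is the V1–V3 correlation, and the standard deviation is the same at both visits. The effect size becomes 0.8 / √(2(1 − r)) for a change score and 0.8 / √(1 − r²) for V3 adjusted for V1.

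| r | Power, V3 value | Power, change | Power, V3 adjusted for V1 |
|---|---|---|---|
| 0.3 | 81% | 67% | 84% |
| 0.5 | 81% | 81% | 90% |
| 0.7 | 81% | 95% | 98% |

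The choice of form therefore matters for power. Over this range the adjusted analysis is the strongest of the three.

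**6. Score definitions.** The WMFT section defines functional ability as a sum from 0 to 75 but gives its important difference as 0.2–0.4 points, at most 0.4 / 75 = 0.5% of the range. A mean over 15 items scored 0 to 5 would fit that figure better, though this is an inference. The same section defines a median time score and then refers to mean time. That could be the group mean of patients' medians, but the text does not say so.

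**The case against.** The strongest counter-argument is that no section says two primary tests will be run. The sentence naming two scores goes on to state what differences would be clinically important; it guides interpretation and is not a testing rule. The Sample size, Statistical method and primary analysis sections all treat the WMFT as one quantity with one comparison, and the primary time point is 3 months throughout. An analysis plan that is not shown could name the score.

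Much of this stands. A reader might infer that two scores are each tested at 0.05, so that the stated alpha and power already fail. The text only implies two tests, and if one score in one form is pre-named, 5% and 80% both hold. A reader might also count all four scores as competing primary tests, but nothing puts the strength scores in the primary analysis. Nor do the documents plan to test both a V3 value and a change. Finally, one might prefer functional ability because median time saturates. The median reaches 120 s if 8 or more of the 15 items are not completed and are scored at the cap, but the documents do not show how often that would happen.

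What does not stand is the appeal to an analysis plan. The sentence is expressly about the primary analysis, it covers two scores, and it calls them changes, while the statistical sections name no score and compare at V3. That is a conflict within the document shown.

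**Conclusion.** The point holds as an unfixed primary endpoint: neither the WMFT score nor its form is settled, and the sections disagree. The sample-size arithmetic is correct, but it applies only to one test of one pre-named score. The type I error range (7.0% to 9.75%) and the joint power range (65% to 76%) describe what would follow if both scores were tested at 0.05. They rest on an assumed correlation of 0 to 0.9 between the scores and, for power, on d = 0.8 for both. Within that range, testing both at 0.05 does not preserve 5% alpha and 80% power together: an either rule loses the first and a both rule loses the second. Because the main claim depends on this choice, it should be settled before unblinding.

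**What to change.** Name one WMFT score as the sole primary endpoint; which one is for the sponsor to decide. Analyse it at V3 with adjustment for its V1 value, which is already collected. Test the other of the two scores second in a fixed sequence at 0.05, only if the first is significant, and make the two strength scores secondary.

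Align the WMFT, Sample size, Statistical method and primary analysis sections to that choice, and state which quantity the d of 0.8 refers to. Reconcile the score definitions: the 0–75 sum with the 0.2–0.4 point difference, and median time with mean time.

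The cost is a change of wording and the loss of primary status for the second score. The 26 per group and 58 in total stand for d = 0.8 on the named quantity. If that d is on the V3 scale, adjustment for V1 raises power to about 84% to 98% for an assumed V1–V3 correlation of 0.3 to 0.7.

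### The WMFT functional score is defined as a 0–75 sum, but its clinically important difference of 0.2–0.4 points fits only a 0–5 item mean

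*Protocol article*

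**What the plan says.** All the relevant text on score and threshold is in the protocol article, section Wolf Motor Function Test (WMFT), under Primary outcome measure.

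- The test has "15 timed and function based tasks", plus two strength tasks.
- On the rating: "For functional ability scoring, a 6-point ordinal scale is used", with anchors at 0 and 5.
- The resulting scores include "a sum of the function score reflecting the movement quality (0–75), (2) a median time score measuring the movement speed", the latter running from 0 to 120 s. Two strength scores complete the list.
- The importance criterion begins "For our primary outcome analysis, the mean WMFT time and functional ability change scores between the two groups need to be" and gives "1.5–2 s for the timed score and 0.2–0.4 points for the functional ability score", citing reference 47.

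The section Statistical method says "The primary outcome will be the difference between both groups" at V3 on the WMFT and names no sub-score. The functional score may therefore carry the primary result. No item-mean functional score is defined anywhere in the article, and no conversion between sum and mean is given.

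**The concern.** The threshold and the score it is meant to judge do not appear to share a scale. A patient's sum moves in whole points, so 0.2–0.4 is smaller than the smallest change one patient can show. A group mean can differ by a fraction of a point, but a difference that small on a 75-point scale is hard to call clinically important.

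This is the only criterion of clinical importance stated for the WMFT, and it is tied explicitly to the primary outcome analysis. Applied to the score as defined, it would screen out almost nothing. If the scale is settled only after results are known, that choice could decide whether a functional-score difference is described as clinically important.

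**Working it through.** **Inputs.** From the WMFT section: 15 rated items, 0–5 each; functional score 0–75; threshold 0.2–0.4 points. From Sample size: d = 0.8, two-sided 5%, 80% power, 26 per group, 10% loss, 58 recruited. The article gives no SD for the functional sum, so SDs of 5, 10, 15 and 20 points are assumed for illustration.

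**1. The plan's own figures reproduce.** The score range is 15 × 5 = 75, so the sum is what is meant. For d = 0.8, a two-sample t-test needs 25.5, hence 26, per group (power 80.7% at 26). Then 52 / 0.9 = 57.8, hence 58. The threshold appears in none of this.

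**2. Size of the threshold on each scale.**

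| Scale | 0.2 points | 0.4 points |
|---|---|---|
| Sum, 0–75 | 0.2/75 = 0.27% | 0.4/75 = 0.53% |
| Item mean, 0–5 | 0.2/5 = 4% | 0.4/5 = 8% |
| Item-mean value converted to the sum | 0.2 × 15 = 3 points | 0.4 × 15 = 6 points |

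**3. The article's other thresholds.** For the FM-UE: 4.25/66 = 6.4% to 7.25/66 = 11.0% of the scale. For the Box and Block Test: 5/80 = 6.3% to 6/75 = 8.0% of a healthy score. The item-mean reading (4–8%) is of the same order; the sum reading is not.

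**4. How often the threshold is passed with no true effect.** With 26 per group, SE = SD × √(2/26). The probability that the absolute observed difference reaches the threshold c is 2 × [1 − Φ(c/SE)].

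| Assumed SD | SE | c = 0.2 | c = 0.4 | c = 3 | c = 6 |
|---|---|---|---|---|---|
| 5 | 1.39 | 88.5% | 77.3% | 3.1% | <0.1% |
| 10 | 2.77 | 94.3% | 88.5% | 27.9% | 3.1% |
| 15 | 4.16 | 96.2% | 92.3% | 47.1% | 14.9% |
| 20 | 5.55 | 97.1% | 94.3% | 58.9% | 27.9% |

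Counting only differences that favour stimulation halves these figures. For c = 0.2 or 0.4 the chance is then about 39% to 49%.

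**5. Relation to significance.** The smallest significant difference is about 2.01 × √(2/26) × SD = 0.557 × SD, that is 2.8, 5.6, 8.4 and 11.1 points for the four SDs. Every significant result therefore exceeds 0.4 points at any SD above 0.4/0.557 = 0.72.

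**The case against.** The strongest reply is that this is loose labelling, not an error. The paragraph uses one label for the 0–75 sum and another for the score in the threshold sentence. It describes functional ability scoring on a 0–5 scale, and the threshold sentence contains the word mean. If that word denotes an item mean, 0.2–0.4 fits. This reading is plausible and probably explains the figures, but the text does not establish it: mean can equally be the group mean, and the only functional score listed is the sum.

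Second, the practical effect is limited. The exceedance rates in the working ignore significance, and most null trials would report a non-significant result. At SDs above 3/0.557 = 5.4, every significant result also exceeds 3 points, so correcting the lower bound would change no verdict on a significant result. The 6-point bound matters at SDs up to 6/0.557 = 10.8. This stands and limits the consequence. It does not make the written threshold usable.

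Several stronger inferences are tempting but unsupported:

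- **That the primary test or N = 58 is compromised.** Neither uses the threshold.
- **That the time threshold is equally empty.** It is 1.5–2 s on a score in seconds.
- **That a median score with a mean threshold is a contradiction.** A group mean of patients' median times is coherent and is the natural reading; a clarification is enough.
- **That giving a range is a fault.** The article does the same for the FM-UE and the Box and Block Test, and nothing makes the range a pass/fail rule.
- **That d = 0.8 and the threshold together imply a particular SD.** The plan never links them; it bases d on earlier effect sizes.

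**Conclusion.** The point holds for the functional score. As written, the importance threshold is 0.27–0.53% of the defined scale and below one step on one item, so almost any group difference in that score would pass. This is a mismatch between two statements that the article makes, not detail left to a fuller document.

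It affects interpretation only; type I error, power and sample size are untouched. The scale percentages follow from the article alone. The exceedance rates rest on the assumed SDs of 5–20 points and a normal approximation. That 0.2–0.4 came from an item-mean scale, and hence that the sum threshold should be 3–6 points (15 times larger), is inferred from the arithmetic; the cited source is not at hand to confirm it.

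**What to change.** First check which scale reference 47 used for functional ability. Then, before unblinding, put score and threshold on that one scale. If the source confirms the item mean, either:

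- define functional ability as the mean of the 15 items (0–5) and keep 0.2–0.4 points; or
- keep the 0–75 sum and state the threshold as 3–6 points.

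The two are equivalent. In the same edit, state that mean time in the threshold sentence is the group mean of patients' median times, if that is intended.

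The cost is about two sentences. Data collection, the planned test and the sample size do not change.
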